### Follow-up

All participants will be followed up regularly as per schedule (Table 2). Biopsy or PET-CT would be done when it is necessary to diagnose recurrence.

**Table 2 Tab2:** Trial schedule

Measures	M1	M3	M6	M9	M12	M18	M24	M30	M36
Physical examination	×	×	×	×	×	×	×	×	×
Blood test	×	×	×	×	×	×	×	×	×
CEA	×	×	×	×	×	×	×	×	×
CA 19-9	×	×	×	×	×	×	×	×	×
CT of chest			×		×	×	×	×	×
CT/MRI of abdomen and pelvis			×		×	×	×	×	×
Colonoscopy			×		×	×	×	×	×
IIEF-5	×	×	×	×	×				
FSFI	×	×	×	×	×				
IPSS	×	×	×	×	×				

*CA* cancer antigen, *CEA* carcinoembryonic antigen, *CT* computed tomography, *FSFI* Female Sexual Function Index, *IIEF* International Index of Erectile Function, *IPSS* International Prostate Symptom Score, *M* month*, MRI* magnetic resonance imaging

### Data collection and management

We have invited more than 10 large medical centers, which have developed experienced LLND surgery in China, to participate in this trial. We have made universal standards including inclusion and exclusion criteria, nCRT, and TME + LLND standard for all units. In order to obtain good-quality monitoring, we have hired a professional clinical research company to organize and manage the work of all participant units. A Case Report Form is made for each participant to record their data.

### Dropping out

When this trial begins, a participant can drop out of this trial even if written informed consent has been signed if: (1) the participant decides to refuse for any reason, (2) unacceptable adverse events are experienced, (3) an investigator withdraws the participant for that participant’s benefit, (4) a participant receives other treatment, such as biological immune therapy, which is not approved in this trial, (5) a participant becomes pregnant in the process of this trial, and (6) the compliance of the participant is poor.

### Safety and adverse effect

All adverse events must be carefully recorded and reported, including nCRT complications and perioperative complications. All severe adverse events in this trial should be reported every 6 months and adverse events which are life-threatening should be recorded and reported within 24 h.

### Sample size and statistical analysis

Our trial aims to demonstrate that LLND could decrease the 3-year local recurrence rate of low rectal cancer patients with suspicion of LLN metastases. Based on previous studies, we assume that the 3-year local recurrence rate for patients with suspicion of LLN metastases who do not undergo LLND is 15% [13–16], and LLND is expected to show a reduction of 7 percentage points. G*Power 3.1 is used to calculate the sample size. A statistical power of 0.80 and a significance level of 0.05 are chosen, and we assume that there will be a 10% dropout rate. Therefore, 512 patients are needed in this specific trial (256 patients in each group).

All participants in this trial will be analyzed using the intention-to-treat analysis. The chi-square test and Student’ *t* test will be used to compare categorical data and continuous data for the two groups, respectively. The 3-year local recurrence rate, the primary endpoint of this trial, will be analyzed using the Kaplan-Meier method, as well as OS and DFS. In addition, based on different characteristics (such as age, sex, tumor stages, etc.), which can identify the influence of competing risk factors, the Cox proportional hazards (PH) regression model will be tested if Schoenfeld Residuals Analysis confirms PH assumption validation. Otherwise, an alternative extended Cox PH model will be used. SPSS 21.0 (SPSS Inc., Chicago, IL, USA) will be used for all statistical analyses, and a *P* value < 0.05 is considered significant.

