## Discussion

Currently, the hot issue of the treatment of LLN in advanced rectal cancer patients is still being debated in different regions. Eastern countries, especially Japan, favor LLND following TME; however, Western countries believe that nCRT and TME is recommended, and LLDN is added only when a LLN is preoperatively diagnosed as metastatic. Actually, preoperatively enlarged LLNs are not common and only a small proportion of LLDs with a maximum short-axis diameter ≥10 mm, or with a spiculated or indistinct border, or a mottled heterogenic pattern are diagnosed as metastatic [23]. The remaining large proportion of LLNs are underdiagnosed as being metastatic and often confuse surgeons’ treatment strategy. Thus, our trial pays particular attention to this stratification of suspicious LLNs, assessing the efficacy and safety of the LLND in advanced rectal cancer patients.

Another issue we have considered in our trial is the randomization time. In our trial, we randomly allocated participants before nCRT rather than after nCRT. Because LLN metastases are commonly diagnosed before nCRT by their features on pelvic MRI or CT and when chemo-radiation has achieved its effect, the treatment-sensitive regions of any enlarged LLNs will have decreased in size which may confuse the randomization if allocation is performed after nCRT.

This trial is the first randomized controlled trial to investigate the role of LLND in reducing local recurrence rates for low advanced rectal cancer patients with suspicion of LLN metastases. If the efficacy of LLND is verified, which reduces the local recurrence rate from 15% to 8%, LLND can be recommended as a new standard strategy for low advanced rectal cancer patients with suspicion of LLN metastases.

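### 512 patients do not give the stated 80% power: 256 per arm is the one-sided 5% size with nothing added for dropout, and two-sided power after 10% loss is about 65%

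*Protocol article*

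**What the plan says.** The Sample size and statistical analysis section of the protocol article gives a complete calculation:

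- Control rate: 3-year local recurrence in patients "who do not undergo LLND is 15"%.
- Effect: "LLND is expected to show a reduction of 7 percentage points", hence 8% with LLND. The Discussion confirms this by describing a verified benefit as one "which reduces the local recurrence rate from 15% to 8"%.
- Error rates and loss: "A statistical power of 0.80 and a significance level of 0.05 are chosen, and we assume that there will be a 10% dropout rate".
- Result: "Therefore, 512 patients are needed in this specific trial (256 patients in each group").

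G*Power 3.1 is named as the software, but not the procedure used within it. Sidedness is not stated. For the analysis, the same section names the chi-square test for categorical data, Kaplan-Meier for local recurrence, OS and DFS, and Cox regression, and a P "value < 0.05 is considered significant". The Randomization and blinding section gives 1:1 allocation.

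**The concern.** All the inputs are printed, so the result can be checked, and 256 per arm looks too small for a fall from 15% to 8% at two-sided 5% with an allowance for dropout. If so, the trial lacks the power it claims. That matters because the Discussion ties a practice recommendation to verifying this very reduction. A reader told that the trial had 80% power could take a non-significant result as evidence against LLND, when the real chance of missing the assumed effect is well above 20%.

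**Working it through.** **Inputs** (Sample size section; allocation from Randomization and blinding): p1 = 0.15, p2 = 0.08, mean p = 0.115, difference 0.07, power 0.80 (z = 0.8416), alpha 0.05, dropout 10%, 1:1. Sidedness is not given, so both readings are computed: z = 1.6449 one-sided, 1.9600 two-sided.

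**Formula, per arm (pooled variance under the null):**

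n = [z_alpha × √(2 × 0.115 × 0.885) + z_beta × √(0.15 × 0.85 + 0.08 × 0.92)]² / 0.07²

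The two square roots are 0.4512 and 0.4484.

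**Reproducing the stated figure.** One-sided 5%: (0.7421 + 0.3774)² / 0.0049 = 255.8, so 256 per arm and 512 in total. This matches the stated number exactly, before any dropout is added.

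**What the stated inputs give:**

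| Test | Per arm, no dropout | Per arm, with 10% dropout (n / 0.9) | Total with dropout |
|---|---|---|---|
| One-sided 0.05 | 256 | 285 | 570 |
| Two-sided 0.05 | (0.8843 + 0.3774)² / 0.0049 = 324.9, so 325 | 362 | 724 |

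**Other formulas.** Per arm before dropout:

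- Unpooled variance: 254 one-sided, 323 two-sided.
- Arcsine: 252 and 319.
- Continuity-corrected: 284 and 353.

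Event-based totals before dropout are about 487 and 617 (Schoenfeld) and 522 and 661 (Freedman). None of these gives 512 once 10% dropout is included. The closest is one-sided Schoenfeld, at about 536 to 541 depending on how the loss is added.

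**Power that 512 gives.** Power = Φ{[0.07√n − z_alpha × 0.4512] / 0.4484}. With 10% lost, 256 × 0.9 = 230.4, taken as 230 per arm.

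| | 256 per arm (no loss) | 230 per arm (10% loss) |
|---|---|---|
| Two-sided 0.05 | Φ(0.526) = 70.0% | Φ(0.395) = 65.4% |
| One-sided 0.05 | Φ(0.843) = 80.0% | Φ(0.712) = 76.2% |

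Exact binomial power of the uncorrected two-sided test is close to this: 70.6% and 66.3%.

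**Log-rank approximation.** HR = ln(0.92) / ln(0.85) = 0.513, so |ln HR| = 0.667. Power = Φ(√d / 2 × 0.667 − z_alpha).

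- 460 evaluable: d = 460 × 0.115 = 52.9 events. Power is 68.0% two-sided, 78.3% one-sided.
- 512 evaluable: d = 58.9 events. Power is 72.6% two-sided, 82.0% one-sided.

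**Detectable effect.** With 230 per arm and a two-sided test, 80% power is reached only for 15% versus 6.9%, a reduction of 8.1 points rather than 7.

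**The case against.** Four points can be made for the plan.

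1. **Sidedness is inferred.** The article never states it, the aim is worded directionally, and the exact match at 255.8 suggests that a one-sided calculation was run. If that was intended, the only arithmetic error is the missing dropout step, and the shortfall is 2 to 4 points (78% log-rank, 76% two-proportion). This is fair as to the size of the shortfall. But a directional aim does not declare a one-sided test, and an unqualified P < 0.05 with chi-square, Kaplan-Meier and Cox analyses is ordinarily two-sided.

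2. **65% is the low end.** It treats dropouts as giving no information, whereas Kaplan-Meier analysis by intention to treat uses their follow-up until loss. This also stands in part. The two-sided range is about 65% to 70% for two proportions and 68% to 73% for the log-rank test. Even full recovery of the lost information does not bring two-sided power near 80%. Only a one-sided log-rank test that recovers much of that information would reach 80%, and the article declares no such test.

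3. **Correcting the text leaves the trial underpowered.** True. With recruitment open, the sponsor could also re-size. That is a larger decision; the wrong statement needs correcting either way.

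4. **DFS is also named as a primary outcome and is not sized at all.** That is a separate matter and does not affect this calculation.

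**Conclusion.** The point holds. The figure of 512 is the one-sided 5% two-proportion size without the dropout allowance that the text says was assumed. Under a two-sided 5% test, which is the natural reading, power for 15% versus 8% is 70% with no loss and about 65% after 10% loss (73% and 68% by the log-rank approximation). The chance of missing the assumed effect is thus about 27% to 35%, against the stated 20%. Under a one-sided 5% test, power after the planned loss is 76% (78% log-rank).

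The after-loss figures assume that lost patients contribute nothing, and the log-rank figures assume proportional hazards and a mean event rate of 11.5%. That a one-sided calculation was run is an inference from the exact match. The conclusion does not need it: no formula tried gives 512 with 10% dropout included, on either reading.

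**What to change.** Correct the sample-size paragraph; enrolment need not change.

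- State that the test of local recurrence is two-sided at 0.05, and name the G*Power procedure.
- State that 512 randomised patients, with 10% lost (about 460 evaluable), give about 65% power for 15% versus 8%, and 70% with no loss. If the log-rank test is the planned comparison, the figures are about 68% and 73%.
- State that 80% two-sided power after loss exists only for a reduction of about 8 points (15% versus 6.9%).
- If a one-sided 0.05 test was intended, declare it and give the power after dropout as about 76%.
- Preferably also commit to reporting the primary result with its confidence interval, so that a non-significant P value is not read as no benefit. This is secondary to correcting the numbers.

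The cost is wording in the protocol and SAP, and a less favourable stated power. Keeping the 80% claim at two-sided 5% would instead need 724 patients, that is 724 − 512 = 212 more; whether to re-size is for the sponsor to decide.

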Despite this, existing retrospective cohorts mainly focus on all middle/low advanced rectal cancer patients, not the specific individuals with suspicion of LLN metastases. And those results indicate almost no differences in local recurrence and overall survival, except for longer operation time, more blood loss, and more perioperative complications for LLND [7–9, 18]. A Korean report enrolled 900 advanced rectal cancer patients with preoperative swollen LLNs, which showed that the recurrence rate was associated with the diameter of the LLNs [16]. However, there is no strict prospective randomized controlled study on the comparison of TME + LLND and TME for low rectal cancer with suspicion of LLN metastases after nCRT. Thus, the objective of this study is to assess the efficacy and safety of LLND for low rectal cancer patients with suspicion of LLN metastases (TME + LLND versus TME). Furthermore, the risk factors (such as radiologic factors, pathologic factors, and serum protein) to predict local recurrence and overall survival will be further investigated.

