### Intervention

After randomization, all participants will firstly receive a cycle of 5-fluorouracil with oxaliplatin therapy (FOLFOX) or capecitabine (Xeloda) with oxaliplatin therapy (XELOX). Subsequently, radiotherapy with 50.4 Gy is administered in 28 separate doses. Next, three cycles of FOLFOX or XELOX will be continued. About 3 to 4 weeks later, patients allocated to the TME group will undergo standard TME surgery solely, while patients allocated to the TME + LLND group will undergo standard TME surgery plus LLND. The extent of LLND includes bilateral LLND (lymph node groups 263P, 263D, and 283). If the short-axis diameter of the external iliac or common iliac lymph nodes is beyond 6 mm, lymph node groups 293, 273, and 280 will be dissected. Unilateral LLND will be done only when the center of the rectal tumor is limited to a single side (not beyond the midline) and the contralateral lymph nodes are not enlarged. Adjuvant chemotherapy, consistent with the preoperative scheme in every patient, will be continued until reaching eight cycles.

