### Outcomes

The primary outcomes of this trial are the 3-year local recurrence rate and 3-year disease-free survival (DFS). The local recurrence is defined as recurrent disease in the pelvis or at the incision and DFS is defined as the time of surgery to the recurrence or end of follow-up. It is diagnosed using the following methods: (1) histological confirmation by biopsy, (2) confirmation by positron emission tomography-computed tomography (PET-CT), (3) CT/magnetic resonance imaging (MRI) shows that there is a mass in the pelvis which is growing with/without symptoms.

The secondary outcomes include 3-year overall survival (OS) and disease-free survival (DFS) at 3 years post surgery, sexual and urinary function at 1 year post surgery, and perioperative outcomes. OS is defined as the time of surgery to the date of death from any cause or the date of follow-up. Sexual function for men and women is assessed by using the International Index of Erectile Function-5 scoring system (IIEF-5) and the Female Sexual Function Index (FSFI), respectively [20, 21]. Urinary function is assessed by using the International Prostate Symptom Score (IPSS) [22]. Perioperative outcomes include operation time, intraoperative blood loss, intraoperative transfusion, incision length, intraoperative complications, time to first flatus, time to liquid diet intake, postoperative hospitalization days, postoperative complications, and mortality.

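### The intention-to-treat rule is stated for all participants without setting surgical harm apart, so patients who never have LLND can count in the LLND arm's harm rate and shrink its absolute excess

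*Protocol article*

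**What the plan says.** The section on sample size and statistical analysis states: "All participants in this trial will be analyzed using the intention-to-treat analysis". It then assigns the chi-square test to categorical data and the t test to continuous data for the two groups. No outcome is exempted from the rule.

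The Discussion gives the time of allocation: "In our trial, we randomly allocated participants before nCRT rather than after nCRT". The Intervention section agrees: "After randomization, all participants will firstly receive a cycle of 5-fluorouracil with oxaliplatin therapy", followed by 28 radiotherapy fractions and three more cycles. Surgery, the first step at which the arms differ, comes after a further wait: "About 3 to 4 weeks later, patients allocated to the TME group will undergo standard TME surgery solely". The section on dropping out lists six routes by which a participant may leave, among them refusal, adverse events and withdrawal by an investigator.

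Safety is an aim in its own right. The Background says that "the objective of this study is to assess the efficacy and safety of LLND for low rectal cancer patients" with suspected lateral node metastases. The secondary outcomes carry that aim: "Perioperative outcomes include operation time, intraoperative blood loss, intraoperative transfusion, incision length, intraoperative complications", then recovery measures, postoperative complications and mortality, with sexual and urinary function at 1 year.

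**The concern.** Intention-to-treat suits recurrence, DFS and OS, where the question is what follows from a policy of offering LLND. For surgical harm, readers also want to know what the added dissection does to a patient who has it. A patient allocated to LLND who has TME alone carries no risk from LLND but counts as an LLND patient. A patient who is never operated on counts as free of operative complications. Both lower the LLND arm's rate. For efficacy, a bias towards no difference is cautious; for harm it favours the new procedure.

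The Background names longer operations, more blood loss and more perioperative complications as the known price of LLND, and the Discussion foresees LLND as a new standard if recurrence falls as hoped. An understated price would enter that decision directly.

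**Working it through.** **Figures in the plan.** The article gives no complication rate, no expected share of patients who will miss LLND and no power for harm, so there is no harm figure to reproduce. It gives 256 patients per group and 10% dropout; 256 × 0.90 = 230.4, taken as 230 per arm. All complication and switching rates below are assumptions.

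**Which outcomes can be diluted.**
- Complications and operative mortality (yes/no): by unoperated patients and by patients who have TME alone.
- Function at 1 year after surgery: by patients who have TME alone. Unoperated patients have no such value.
- Operation time, blood loss, incision length and similar measures: they do not exist without surgery, so unoperated patients cannot dilute them, and an analysis of all participants cannot be carried out on them literally.

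**Case 1: the operation changes.** Let p_T and p_L be the true rates with TME and with TME + LLND, and Δ = p_L − p_T. Let f be the share of the LLND arm that has TME alone and c the share of the TME arm that has LLND.

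- Observed TME arm: p_T + cΔ
- Observed LLND arm: p_L − fΔ
- Observed difference: Δ(1 − f − c)

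With p_T = 20%, p_L = 30%, f = 10% and c = 5%:

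- TME arm: 20 + 0.05 × 10 = 20.5%
- LLND arm: 30 − 0.10 × 10 = 29.0%
- Difference: 10 × 0.85 = 8.5 points

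Power (two-sided 5%, pooled variance under the null) is Φ[(Δ − 1.96·SE0)/SE1], with n = 230 per arm.

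- No switching: SE0 = √(0.25 × 0.75 × 2/230) = 0.0404; SE1 = √[(0.20 × 0.80 + 0.30 × 0.70)/230] = 0.0401; power = Φ(0.52) = 0.70.
- With switching: SE0 = √(0.2475 × 0.7525 × 2/230) = 0.0402; SE1 = √[(0.205 × 0.795 + 0.29 × 0.71)/230] = 0.0400; power = Φ(0.15) = 0.56.

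Range under other assumptions:

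| True rates | n per arm | f / c | Observed difference (points) | Power |
|---|---|---|---|---|
| 20% vs 30% | 230 | 0 / 0 | 10.0 | 0.70 |
| 20% vs 30% | 230 | 10% / 5% | 8.5 | 0.56 |
| 20% vs 30% | 230 | 20% / 5% | 7.5 | 0.47 |
| 10% vs 18% | 230 | 0 / 0 | 8.0 | 0.70 |
| 10% vs 18% | 230 | 10% / 5% | 6.8 | 0.56 |
| 25% vs 35% | 256 | 0 / 0 | 10.0 | 0.70 |
| 25% vs 35% | 256 | 5% / 0 | 9.5 | 0.65 |
| 25% vs 35% | 256 | 10% / 0 | 9.0 | 0.61 |
| 25% vs 35% | 256 | 20% / 0 | 8.0 | 0.51 |

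**Case 2: equal shares of both arms are never operated on.** With 10% unoperated and counted as free of complications, 20% and 30% become 0.9 × 20 = 18.0% and 0.9 × 30 = 27.0%. The difference falls to 9.0 points and the risk ratio stays at 27/18 = 1.5. Power is 0.69 with 256 per arm. Among operated patients only (230 per arm) the difference is 10.0 points and power 0.70. Here the absolute difference is understated and power hardly changes.

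**The case against.** The strongest reply is that the statement is correct for a randomised trial and excludes nothing. A reader might infer that harm will be analysed by intention-to-treat and in no other way. The article does not say so; it is condensed, and a full protocol or analysis plan may define an operated or as-treated set. That stands, so the point concerns what the stated rule does if followed as written.

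A reader might also infer that nCRT toxicity is pooled with surgical events in one between-arm test. The safety section says "All adverse events must be carefully recorded and reported, including nCRT complications and perioperative complications", but this concerns recording and reporting, names the two as separate items and sets no pooled comparison. That reading is not supported.

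The Intervention section assigns one operation per arm, and no section foresees or quantifies crossover. This also stands: the rates f and c are assumptions. They are plausible because surgeons and investigators know the allocation during a long preoperative course with several ways out.

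Finally, grouping by operation performed brings its own bias. Frailty, progression or difficulty at surgery may decide who ends with TME alone, and this could move the harm comparison either way. It is a good reason to show that analysis beside intention-to-treat and not in its place.

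**Conclusion.** The point holds as a modest weakness in a stated rule. Non-receipt of LLND shrinks the absolute excess of yes/no surgical harms and, where patients have TME alone, of impaired 1-year function. In the main example a 10.0-point excess appears as 8.5 points, with power about 0.56 in place of 0.70. With 5% to 10% non-receipt in the LLND arm and no crossover it appears as 9.5 to 9.0 points. These sizes rest wholly on assumed rates.

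A reader might conclude that the trial will find no difference in harm. The figures do not support that: most of the excess remains in every case shown, and equal non-operation leaves the risk ratio intact. Intention-to-treat for recurrence, DFS and OS is not in question.

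The eligibility table adds an uncertainty. It lists performance of mesorectal excision and an R0 resection as criteria, yet both are known only after randomisation. If they are applied as eligibility criteria, unoperated patients would leave the analysis, contrary to the rule for all participants. The article does not say which governs.

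**What to change.** Keep intention-to-treat for recurrence, DFS and OS. For perioperative outcomes, operative mortality and 1-year sexual and urinary function, state that:

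- the analysis is also done in patients who had surgery, once by allocated arm and once by operation performed (TME, or TME + LLND);
- events are counted from the date of surgery;
- the intention-to-treat result is shown beside it where the outcome exists;
- the number in each arm who did not receive the assigned operation is reported, with reasons.

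Reconcile this with the eligibility criteria that are known only after randomisation, and say whether patients who fail them stay in the intention-to-treat population.

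The cost is a sentence or two and an extra set of tables. It assumes that the case report form captures the operation performed and its date; the article does not list the form's contents. The article reports enrolment still under way, so the wording could be settled before analysis. The drawback is that neither the operated nor the as-operated comparison is fully randomised, and the latter may be confounded by the reasons why an operation changed.

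### Kaplan-Meier for the primary 3-year local recurrence rate overstates the absolute risk in both arms, because deaths without local recurrence would be censored; the test of the cause-specific hazard is unaffected

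*Protocol article*

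**What the plan says.** The protocol article, section Sample size and statistical analysis, gives one estimator to three endpoints: "The 3-year local recurrence rate, the primary endpoint of this trial, will be analyzed using the Kaplan-Meier method, as well as OS and DFS".

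The Outcomes section fixes the events:

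- Local recurrence: "The local recurrence is defined as recurrent disease in the pelvis or at the incision". Death is not part of it.
- DFS, also primary: "DFS is defined as the time of surgery to the recurrence or end of follow-up". Death is not named here either.
- OS: "OS is defined as the time of surgery to the date of death from any cause". This is the only one of the three in which death is an event.

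The only appearance of competing risk is in the description of the Cox model, where patient characteristics such as age, sex and tumour stage are introduced with "which can identify the influence of competing risk factors, the Cox proportional hazards (PH) regression model will be tested". These are covariates, not competing events. The article names no cumulative incidence method.

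The target is set on an absolute scale. For the control arm, "we assume that the 3-year local recurrence rate for patients with suspicion of LLN metastases who do not undergo LLND is 15" per cent, and "LLND is expected to show a reduction of 7 percentage points". The Discussion ties a change in standard practice to a fall from 15% to 8%.

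**The concern.** Death without local recurrence rules out a later local recurrence. Kaplan-Meier treats a patient censored at death as someone who could still recur at the same rate as those who remain at risk. One minus Kaplan-Meier therefore estimates the local recurrence risk in a hypothetical setting where nobody dies of anything else. It does not estimate the share of operated patients who have a local recurrence within 3 years.

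The endpoint is phrased as a 3-year rate, and the Discussion judges success by two absolute percentages and the gap between them. If the published rates come from one minus Kaplan-Meier, both are too high. The gap is also off, by an amount that depends on mortality in each arm. Equal mortality cannot be taken for granted: OS is an outcome in its own right, perioperative mortality is recorded, and the Background reports more perioperative complications with LLND.

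**Working it through.** **Inputs from the article.** Control 3-year local recurrence is 15% and the reduction is 7 points, so the LLND arm is 15 - 7 = 8%, which matches the Discussion. There are 256 patients per arm, with 10% dropout. The article reports no Kaplan-Meier rate, so there is no figure of its own to reproduce on this point.

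**Assumed inputs.** The article gives no rate of death without local recurrence. Let *d* be its 3-year cumulative incidence, taken as 5-20%. Cause-specific hazards are constant over the 3 years.

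**Formula.** Let *c* be the true 3-year cumulative incidence of local recurrence. The chance of neither event by 3 years is 1 - c - d, so the total cumulative hazard is -ln(1 - c - d). With constant hazards, local recurrence takes the share c/(c + d). Censoring deaths leaves only that share, so

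1 - KM = 1 - (1 - c - d)^(c/(c + d)).

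**Worked case, d = 5%.**

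- TME: 1 - 0.80^(0.15/0.20) = 1 - 0.80^0.75 = 0.1541.
- TME + LLND: 1 - 0.87^(0.08/0.13) = 0.0821.
- Difference: 7.2 points instead of 7.0.

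**Equal death rates in both arms (true values 15%, 8%, difference 7.0 points).**

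| d | 1 - KM, TME | 1 - KM, TME + LLND | Difference (points) |
|---|---|---|---|
| 5% | 15.4% | 8.2% | 7.2 |
| 10% | 15.9% | 8.4% | 7.4 |
| 15% | 16.3% | 8.7% | 7.6 |
| 20% | 16.9% | 9.0% | 7.9 |

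**Unequal death rates.**

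| d, TME / TME + LLND | 1 - KM, TME | 1 - KM, TME + LLND | Difference (points) |
|---|---|---|---|
| 5% / 15% | 15.4% | 8.7% | 6.7 |
| 10% / 20% | 15.9% | 9.0% | 6.9 |
| 10% / 5% | 15.9% | 8.2% | 7.6 |
| 15% / 5% | 16.3% | 8.2% | 8.1 |
| 20% / 10% | 16.9% | 8.4% | 8.4 |

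While the arms differ by no more than 10 points within the 5-20% range, the difference stays between about 6.7 and 8.4. The cumulative incidence function targets 15%, 8% and 7.0 points in every row of both tables.

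**Effect on a hazard comparison.** The cause-specific hazard ratio is ln(1 - KM risk, LLND)/ln(1 - KM risk, TME). At d = 5% this is ln(0.9179)/ln(0.8459) = 0.512; at d = 20% it is ln(0.9104)/ln(0.8314) = 0.508. Censoring deaths is the correct way to estimate this quantity, so it carries no such bias.

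**Scale against sampling error.** The variance term is 0.15 × 0.85 + 0.08 × 0.92 = 0.2011. The standard error of the difference is √(0.2011/256) = 2.8 points with all patients, and √(0.2011/230) = 3.0 points after 10% dropout (0.9 × 256 ≈ 230). The equal-mortality shift of 0.2 to 0.9 points is at most about a third of one standard error.

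**The case against.** The strongest reply is that the effect is small and partly inferred. The article does not write out how deaths are handled; censoring follows from Kaplan-Meier applied to an event definition without death. Every size above rests on an assumed death rate. At 5-10% equal mortality the difference moves by 0.2 to 0.4 points, under one sixth of a standard error. All of this stands, and it limits the weight of the point. It does not change the direction: any death without local recurrence, once censored, pushes one minus Kaplan-Meier above the true cumulative incidence.

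Three stronger readings go beyond the document:

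- A reader might infer that the primary hypothesis test is invalid. It is not. A log-rank or Cox comparison with such deaths censored is a valid test of the cause-specific hazard. Gray's test is not an automatic replacement either, because it responds to mortality: more early deaths in one arm could make that arm look better on recurrence.
- A reader might infer that the planning rates and the planned analysis are on different scales. The 15% comes from cited studies that are not shown, and the article does not say how they estimated it. If they used Kaplan-Meier, the two scales agree.
- A reader might infer a much larger bias by supposing that patients leave follow-up at distant relapse. The Follow-up section keeps all participants on schedule to month 36, and Dropping out does not list distant relapse. Its clause on unapproved other treatment could catch some such patients, but that is conjecture.

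**Conclusion.** The point holds for the absolute 3-year local recurrence rates and their difference, and no further. Both rates would be overstated: by 0.4 to 1.9 points in the TME arm and 0.2 to 1.0 in the TME + LLND arm, for 5-20% competing death and constant hazards. With equal mortality the difference is slightly widened. With unequal mortality it can be widened or narrowed, so the direction of its error cannot be known in advance.

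These sizes depend on assumed death rates and on deaths being censored, which the article implies but does not state. The bias is modest beside sampling error. The correction is still worth making, because the primary endpoint and the success statement are both worded as absolute 3-year rates.

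**What to change.** In Sample size and statistical analysis, replace Kaplan-Meier for local recurrence with the cumulative incidence function (Aalen-Johansen), taking death without local recurrence as the competing event. Report the 3-year estimate per arm and their difference with a 95% confidence interval. Keep the cause-specific log-rank or Cox comparison alongside, and state that deaths are censored in it.

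Keep Kaplan-Meier for OS. Keep it for DFS only if the Outcomes definition is amended so that death counts as a DFS event; as now worded, DFS has the same problem. Reword "which can identify the influence of competing risk factors" so that covariates are not described in the language of competing events.

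The cost is a change of analysis text and possibly software beyond the SPSS 21.0 named for all analyses. Reported recurrence rates will be slightly lower than Kaplan-Meier would give. No new data are needed, since dates of death are already required for OS.
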